**Figure 2 fig2:**
[figure not shown]
**Primary end points.** Primary short-term and primary long-term end points. CFR, coronary flow reserve, CMD, coronary microvascular dysfunction; EKG, electrocardiogram; IMR, index of microcirculatory resistance; INOCA, ischemia and nonobstructive coronary arteries; IVUS, intravascular ultrasound; N/A, not applicable; OCT, optical coherence tomography; QCA, quantitative coronary angiography; VSA, vasospastic angina.

Physiologic assessment will be performed with the CoroFlow Cardiovascular System and PressureWire X guidewire (Abbott Vascular) per the instructions for use. A PressureWire X guidewire will be advanced at least 6 cm or two-thirds of the way down the vessel. Any contrast will be cleared from the catheter, and the temperature will be zeroed. Resting Pd/Pa and resting full cycle ratio will be recorded. Baseline saline thermodilution will be performed and repeated 3 times to determine the baseline mean transit time (T_mn_). Adenosine will be administered intravenously at 140 μg/kg/min. During hyperemia, thermodilution will be repeated 3 times to determine the hyperemic mean transit time (T_mn-hyp_). Coronary flow reserve (CFR), index of microcirculatory resistance (IMR), and fractional flow reserve (FFR) will be recorded (Figure 2).

Intracoronary imaging will be performed with optical coherence tomography (OCT) or intravascular ultrasound (IVUS) according to the acquisition guidelines. Imaging should be performed on the vessel that underwent guidewire assessment using an automated pullback for a minimum of 54 mm.

### Core laboratory analysis

Offline postprocedure analyses will be made by the imaging and physiology core laboratories and include quantitative coronary angiography (QCA) evaluation of all epicardial vessels, quantitative interpretation of IVUS or OCT imaging, resting Pd/Pa, resting full cycle ratio, or other nonhyperemic indices, IMR, CFR, and FFR, and quantitative flow ratio (Medis Medical Imaging).

### Follow-up

All subjects will have clinical follow-up prior to discharge from the index procedure. Changes in medical therapy are at the discretion of the treating provider and will be recorded postprocedure and at all follow-up time points. Screening, procedural, and primary follow-up data collection will occur through the electronic medical record based on the local standard of care, augmented by study-specific telehealth contacts from a centralized call center at 30 days, 6 months, 12 months, and annually through 5 years (Supplemental Table S2). Symptom assessment and patient-reported outcome measures will be completed by the centralized call center at each time point.

### End points

The primary short-term end point is to characterize the prevalence of each INOCA physiologic phenotype and degree of epicardial atherosclerosis (none, mild, moderate) and presence/absence of a myocardial bridge by angiography and IVUS/OCT (Figure 2). The primary long-term end point will be the incidence of MACE, defined as a composite of cardiovascular death, myocardial infarction, hospitalization for cardiovascular causes, or coronary revascularization at a follow-up of 5 years (Figure 2).

#### Secondary end points

Secondary end points are patient-related end points and procedural end points. Secondary patient-related end points include MACE and its components, stroke, progression to obstructive CAD, major bleeding, major vascular complications, angina severity, and patient-reported outcomes (Table 3). Procedural end points include reclassification from preprocedure diagnosis, completion of CFT without device-related serious adverse events or major angiographic complications, and frequency/nature of major angiographic complications (Table 3).

**Table 3 tbl3:** Secondary end points.

**Patient-Related End Points**
The following end points will be reported at all time points, unless otherwise specified: • MACE at all time points not included in the primary end point • Major adverse cardiovascular and cerebrovascular events (MACCE), defined as MACE and/or any stroke (NeuroARC definition) • All-cause, cardiovascular, and noncardiovascular mortality • Myocardial infarction (Fourth Universal Definition) • Stroke (NeuroARC definition) • Revascularization (PCI or CABG) • Hospitalization for cardiovascular causes • Hospitalization for heart failure • Repeat coronary angiography • Progression to obstructive CAD by core laboratory analysis (subject level) • Progression to obstructive CAD by core laboratory analysis (lesion level) • Major bleeding (BARC definition 3-5) • Major vascular complications • Composite of death, myocardial infarction, and stroke • Angina severity assessed by Canadian Cardiovascular Society class or Braunwald Unstable Angina classification • Seattle Angina Questionnaire as a change from baseline • Quality of life assessed by EQ-5D-5L (at 30 d, 6 mo, and 1-5 y) as a change from baseline • Depression assessed by the PHQ-8 questionnaire (at 30 d, 6 mo, and 1-5 y) as a change from baseline • Anxiety assessed by the GAD-7 questionnaire (at 30 d, 6 mo, and 1-5 y) as a change from baseline
**Procedural End Points**
The following end points will be reported in-hospital (or within 48 h of the index procedure): • Reclassification from preprocedure diagnosis (including noncardiac chest pain) • Completion of the interventional diagnostic procedure without device-related serious adverse events or major angiographic complications • Frequency of major angiographic complications (device-related coronary artery dissection [greater than type C], slow or no flow, or perforation)

BARC, Bleeding Academic Research Consortium; CABG, coronary artery bypass grafting; CAD, coronary artery disease; EQ-5D-5L, EuroQol 5 Dimensions – 5 Levels; GAD, Generalized Anxiety Disorder; MACCE, major adverse cardiovascular and cerebrovascular events; MACE, major adverse cardiovascular events (composite of cardiovascular death, myocardial infarction, hospitalization for cardiovascular causes, or coronary revascularization); NeuroARC, Neurologic Academic Research Consortium; PHQ, Patient Health Questionnaire; PCI, percutaneous coronary intervention.

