**Conclusions:**

DISCOVER INOCA is the first prospective study of INOCA patients to integrate anatomic and physiologic measures of disease and correlate them with long-term outcomes. DISCOVER INOCA will report on the prevalence of INOCA phenotypes, the safety of comprehensive invasive CFT, and the impact of testing on diagnoses and medical therapy. Symptoms and cardiovascular adverse events at long-term follow-up will be determined in patients with no obstructive CAD undergoing angiography.

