## Methods

### Study design

DISCOVER INOCA is a prospective, multicenter registry of patients with INOCA evaluated by ICA, intravascular imaging, and physiologic assessment with the CoroFlow Cardiovascular System (Central Illustration). The study is registered at ClinicalTrials.gov (NCT05288361). Participants will be enrolled at up to 10 investigational sites in the United States with prior experience performing CFT. A current list of investigational sites is provided in Supplemental Table S1. Clinical end points will be adjudicated by independent physician review by a provider who is not part of the study team. The relationship of these events to the procedure and physiology assessment protocol will also be adjudicated. Index procedure angiographic data, physiologic assessments, and intracoronary imaging will be analyzed offline by an angiographic core laboratory and intravascular imaging core laboratory (Yale Cardiovascular Research Group).

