### Index procedure

Invasive CFT is intended to be performed as part of the standard of care evaluation for patients who present to the cardiac catheterization laboratory. After excluding the presence of obstructive CAD, the purpose of the procedure is to evaluate coronary vasoreactivity with acetylcholine provocation, physiology with thermodilution, identify myocardial bridging, and describe the burden of atherosclerosis by intravascular imaging (the DISCOVER INOCA index procedure protocol is included as a Supplemental Appendix).

The target vessel for physiologic analysis and intracoronary imaging will be the vessel in which physiologic assessment is clinically indicated or the left anterior descending artery. Coronary angiography will be performed using a standardized acquisition protocol. Angiograms will be acquired in at least 2 projections for each major artery or branch, and the treating physician will record an estimation of stenosis location and severity. The sequence of procedural elements including acetylcholine testing, wire-based testing, and intravascular imaging are at the discretion of the operator and will be recorded.

Coronary vasoreactivity testing will be performed with bolus injection or infusion of escalating doses of intracoronary acetylcholine via a guide catheter. Recommended doses for acetylcholine testing are listed in the Supplemental Appendix. Angiography will be performed after each dose with documentation of electrocardiogram changes and/or symptoms to evaluate for endothelial dysfunction, epicardial coronary vasospasm, and microvascular spasm (Figure 2).

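### The procedural completion end point limits serious adverse events to device-related ones, although the registry says it will report the safety of the whole coronary function test, drugs included

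*Protocol article*

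**What the plan says.** The end point appears twice in the protocol article with the same qualifier. Table 3, under Procedural End Points, has "Completion of the interventional diagnostic procedure without device-related serious adverse events or major angiographic complications". The running text under Secondary end points has "completion of CFT without device-related serious adverse events or major angiographic complications". Table 3 describes the angiographic complications as "device-related coronary artery dissection [greater than type C], slow or no flow, or perforation". The reporting window is the hospital stay or 48 hours from the index procedure.

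The abstract's Conclusions set the aim: the registry will report "the safety of comprehensive invasive CFT, and the impact of testing on diagnoses and medical therapy".

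The Index procedure section shows what the test consists of. On provocation it says: "Coronary vasoreactivity testing will be performed with bolus injection or infusion of escalating doses of intracoronary acetylcholine via a guide catheter". Thermodilution is then repeated under intravenous adenosine. The Discussion lists acetylcholine provocation and thermodilution among the required protocol elements.

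Under Study design, clinical end points go to an independent physician, and "The relationship of these events to the procedure and physiology assessment protocol will also be adjudicated".

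**The concern.** The object of the safety statement is the whole test, and two drugs are part of it. The end point that combines completion with freedom from harm filters serious adverse events by their relation to the device. A serious reaction to acetylcholine or adenosine is related to the drug, so it does not meet that filter. Unless it fails the end point in another way, the patient is scored as having completed the test safely.

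If this figure is later used to describe the safety of CFT, it will partly describe the safety of the wire and catheter. The contribution of provocation and hyperemia will be under-counted. The other two procedural end points do not fill the gap: one concerns reclassification of the diagnosis, the other the frequency of major angiographic complications.

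**Working it through.** **Inputs.** End point and list of angiographic complications: Table 3 and Secondary end points. Safety aim: abstract, Conclusions. Drug components: Index procedure and Discussion. Adjudication: Study design. Sample size: up to 500, from the eligibility section. The article states no expected rate, margin or sample size for this end point, so there is no figure of the plan to reproduce. The exact interval used below is the method the plan names for prevalence. Applied to the plan's prevalence example (n = 500, 10% and 50%), it gives widths of 5.5% and 8.9%, as the Statistical analysis section states.

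**Step 1: apply the definition.** A patient fails if (a) the procedure is not completed, (b) there is a device-related serious adverse event, or (c) there is a major angiographic complication. Otherwise the patient is a success.

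| Event | (a) | (b) | (c) | Score on this end point | Captured elsewhere in Table 3? |
|---|---|---|---|---|---|
| Device-related serious adverse event, test completed | no | yes | – | Failure | Depends on event |
| Drug-provoked event that stops the test | yes | no | – | Failure | Depends on event |
| Acetylcholine-induced slow or no flow, test completed | no | no | unclear | Depends on the reach of the device-related qualifier | Angiographic complications, with the same ambiguity |
| Drug-provoked infarction, test completed, no listed angiographic complication | no | no | no | Success | Yes, and adjudicated for relation to the test |
| Drug-provoked serious arrhythmia, treated, test completed, no listed angiographic complication | no | no | no | **Success** | No category of its own |

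The last row is the gap. The fourth row is a narrower mismatch: the event is reported, but this end point still reads as a safe completion. In the third row the wording leaves the answer open.

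**Step 2: size per event.** One reclassified patient in 500 changes the rate by 1/500 = 0.2 percentage points.

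**Step 3: illustration of the interval.** For x failures in n patients, the exact 95% limits are: lower = Beta quantile 0.025 with parameters (x, n − x + 1), upper = Beta quantile 0.975 with parameters (x + 1, n − x). For x = 0 the lower limit is 0 and the upper is 1 − 0.025^(1/n). With n = 500, and assuming no failure of any other kind:

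| Uncounted drug events (assumed) | Failure rate if counted | Exact 95% CI |
|---|---|---|
| 0 | 0% | 0 to 0.74% |
| 1 | 0.2% | 0.01 to 1.11% |
| 5 | 1.0% | 0.33 to 2.32% |
| 10 | 2.0% | 0.96 to 3.65% |

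In each row the end point as written would report the first line, 0% (0 to 0.74%). With 5 or 10 such events, the rate with drug events counted (1.0% or 2.0%) lies above that upper limit. The counts are assumptions chosen to show scale; nothing in the article supports one row over another.

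**The case against.** Four arguments count against a stronger version of this point.

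1. *A reader might infer that only device-related events can fail the end point.* The text does not support that. Non-completion is a failure whatever its cause. In the list of angiographic complications the qualifier stands before dissection and need not govern slow or no flow, or perforation. Spasm with slow or no flow may well count. Nor does the list set any condition on duration or recovery, so it cannot be said that an episode with restored flow is excluded. This stands, and it limits the gap to serious drug events in completed tests without a listed complication.

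2. *A reader might infer that drug-provoked infarction, stroke or death disappears from the study.* It does not. These are separate patient-related end points in Table 3, and Study design provides for adjudicating clinical end points for their relation to the procedure and the physiology protocol. This also stands. What remains is that such an event does not by itself fail the completion end point, and that serious events outside those categories have no stated route to a procedural safety figure.

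3. *A reader might infer a definite bias, for instance a true 98% reported as 100%.* That would need an event rate the article does not give, every such event to escape the other two failure criteria, and no other failures at all. It is a worst case under assumption, not an estimate.

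4. The end point is secondary and descriptive, the article plans no formal hypothesis testing of secondary end points, and the safety aim is not tied to this one item. The article also condenses a fuller protocol. That lowers the stakes but does not remove the mismatch. The point does not concern an omitted detail: the restriction is written into the end point in both places, and this is the only listed composite of completion and freedom from harm.

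**Conclusion.** The concern holds in a limited form. The serious-adverse-event component is narrower than the aim of reporting the safety of CFT, because it leaves out serious events attributable to acetylcholine or adenosine. Such an event counts as a safe completion when the test is finished and there is no dissection, slow or no flow, or perforation.

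The effect is 0.2 percentage points per event if all 500 patients are enrolled and counted. The total cannot be estimated from the article; the interval figures are illustrations under assumed counts and assume no other failures. The direction is known: any such event makes the completion rate look more favourable. The primary end points are not affected. The wording should be corrected before results on procedural safety are reported.

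**What to change.** Change Table 3 and the Secondary end points text together:

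- Define the end point as completion of CFT with no serious adverse event adjudicated as related to the device or to any component of CFT, including acetylcholine and adenosine, and with no major angiographic complication.
- Extend the relatedness adjudication under Study design, now stated for clinical end points, to all serious adverse events within the procedural reporting window.
- Tabulate device-related, drug-related and angiography-only events separately. Angiography is clinically indicated in these patients in any case, so events due to it alone should not blur a figure meant to describe CFT.
- State whether the device-related qualifier governs slow or no flow and perforation, or dissection only.

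No part of the procedure changes. The cost is a revised definition, one further table and a little more adjudication, with a reported completion rate that may be slightly lower.

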### Statistical analysis

#### Primary short-term end point

The prevalence of the various phenotypes will be estimated using the Exact (Clopper-Pearson) formula. Assuming the prevalence ranges between 10% and 50% in each phenotype, with a sample size of 500, the width of the CI will range from 5.5% to 8.9% (with a maximum interval width of 8.9%) allowing for adequate estimation of the prevalence within each group.

#### Primary end point

The study sample size was calculated to provide adequate power to identify variables associated with primary long-term end point events on the basis of a range of assumptions about the frequency of high-risk characteristics, their predictive accuracy, the overall rate of such events, and the hazard ratio (HR) for the risk factor. For example, if 32% of patients had a high-risk variable, 500 patients would be needed to provide 70% and 90% power to detect a HR of 4.0 for MACE of 3% and 5%, respectively, with a 1-sided alpha of 0.025. With 500 subjects, the minimum HR that will be able to be detected with event rates of 3% and 5% is 3.0 and 2.3, respectively (assuming 32% prevalence of the high-risk factor as noted above).

Baseline variables that are considered clinically relevant or that show a univariate relationship with outcome will be entered into multivariate Cox proportional hazards regression models. Variables for inclusion will be chosen, given the number of events available, to ensure parsimony of the final models. Lesion-level multivariable models will be adjusted for patient effects by means of the marginal Cox model, and nonsignificant variables dropped by backward selection. Statistical analyses will be performed using SAS software version 9.4 (SAS Institute).

Secondary end points will be reported in the overall population and by phenotype using appropriate descriptive statistics. In general, statistics for continuous variables will include mean, median, quartiles, SD, minimum, maximum, and sample size. Binary variables will be summarized using frequencies, percentages, and sample size. No formal hypothesis testing will be performed, and there is no plan to adjust alpha to account for multiple testing of exploratory secondary end points. Subgroup analyses will be performed for all primary and secondary end points for the following subgroups: presentation, categorization of plaque burden, diabetes status, sex, and plaque characterization.

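### The minimum detectable hazard ratios of 3.0 and 2.3 are significance thresholds with only about 50% power, so they overstate what 500 patients can detect

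*Protocol article*

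**What the plan says.** The subsection on the primary end point, under Statistical analysis in the protocol article, says the sample size was chosen to give adequate power to identify variables associated with primary long-term end point events. Its worked example has these parts:

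- Prevalence of the risk factor: "if 32% of patients had a high-risk variable".
- Power: "500 patients would be needed to provide 70% and 90% power to detect a HR of 4.0 for MACE of 3% and 5%, respectively".
- Test level: "with a 1-sided alpha of 0.025".

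The next sentence keeps the sample size, event rates and 32% prevalence, and states the result as a capability: "the minimum HR that will be able to be detected with event rates of 3% and 5% is 3.0 and 2.3, respectively". No power is given for these two hazard ratios, and nothing says that the standard has changed from the 70% and 90% just quoted.

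**The concern.** The two sentences sit uneasily together before any formula is applied. Sample size, prevalence and event rates are the same in both. If a hazard ratio of 4.0 has 70% power at a 3% event rate, a hazard ratio of 3.0 must have less. If 4.0 has 90% power at 5%, then 2.3 must have well under 90%. Yet the smaller values are presented as what the study will be able to detect, in a paragraph that opens by claiming adequate power.

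Finding variables associated with MACE is the third stated aim of the registry. This sentence is the article's most direct statement of how small an association 500 patients can reveal. If the figures are really 50%-power values, a reader planning around them, or judging the registry's later results against them, would credit it with more sensitivity than it has.

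**Working it through.** **Inputs**, all from the subsection on the primary end point: N = 500; prevalence p = 0.32, so p(1 − p) = 0.32 × 0.68 = 0.2176; 1-sided alpha 0.025, so z = 1.96; event rates 3% and 5%. Read as overall proportions, the rates give D = 500 × 0.03 = 15 and D = 500 × 0.05 = 25 events.

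**Formula** (Schoenfeld): power = Φ(√(D·p(1 − p)) × ln HR − 1.96). Here √(15 × 0.2176) = 1.807 and √(25 × 0.2176) = 2.332.

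**Step 1. Reproduce the plan's own figures for a hazard ratio of 4.0** (ln 4 = 1.386).

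- 3%: 1.807 × 1.386 − 1.96 = 0.545, power 70.7% (stated 70%).
- 5%: 2.332 × 1.386 − 1.96 = 1.273, power 89.9% (stated 90%).

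Both reproduce, so the formula and inputs are a sound basis for checking the next sentence.

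**Step 2. Power at the stated minimum hazard ratios.**

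- 3%, HR 3.0 (ln 3 = 1.099): 1.807 × 1.099 − 1.96 = 0.025, power 51.0%.
- 5%, HR 2.3 (ln 2.3 = 0.833): 2.332 × 0.833 − 1.96 = −0.017, power 49.3%.

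**Step 3. Where 3.0 and 2.3 come from.** Inverting the formula gives minimum HR = exp((1.96 + z_power) / √(D·p(1 − p))). At 50% power z_power is 0, which leaves the smallest observed hazard ratio that just reaches significance.

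| Power | 3% (15 events) | 5% (25 events) |
|---|---|---|
| 50% | 2.96 | 2.32 |
| 70% | 3.96 | 2.90 |
| 80% | 4.71 | 3.32 |
| 90% | 6.01 | 4.01 |

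The 50% row rounds to the printed 3.0 and 2.3. The printed 4.0 appears at 70% power for a 3% rate and at 90% power for a 5% rate. All the printed figures thus fit one formula, with the power term absent from the last two.

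**Step 4. Events needed for 80% power at the stated values.** D = (1.96 + 0.842)² / (0.2176 × (ln HR)²). HR 3.0 needs 30 events, against 15 assumed. HR 2.3 needs 52, against 25 assumed. Each is about double.

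**Step 5. Other methods.** Power at HR 3.0 (3% rate) and HR 2.3 (5% rate):

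- Freedman's formula: 60% and 57%.
- Two-proportion test: 59% and 58%.
- Log-rank simulation, 4,000 runs, carried out twice: 57% and 60% for HR 3.0; 56% and 55% for HR 2.3.

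These methods are also more generous to HR 4.0: 79% and 95% by Freedman, 75% and 92% by two proportions, 78% and 93% by simulation. They do not reproduce the plan's 70%, and none brings 3.0 or 2.3 near 80%. Relaxing alpha to 1-sided 0.05 gives only 63% and 62%, and contradicts the stated 0.025.

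**The case against.** The strongest reply is that no printed number is false. The article states no power for 3.0 and 2.3, and the smallest observed hazard ratio reaching significance is a recognised quantity, here correctly calculated. The main justification for the sample size is the hazard ratio of 4.0, which reproduces, and a careful reader can see that smaller effects must have less power. This stands in part: the fault is an unlabelled threshold, not a miscalculated power. It does not clear the sentence, which says what 500 subjects will be able to detect. A true effect at the threshold is detected only about half the time in the plan's own formula.

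It is also fair that the 50% belongs to one approximation, which is rough with 15 events and large hazard ratios. Simulation gives 55% to 60%, so it would be too firm to say that such effects are missed exactly half the time.

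A reader might go further in four ways that the document does not support.

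- **Contradiction with the phenotype prevalences.** The subsection on the primary short-term end point says "Assuming the prevalence ranges between 10% and 50% in each phenotype", which might suggest the power statement should cover 10% prevalence. That range is a precision assumption for phenotype estimates. The 32% is an example for a high-risk variable. They are different quantities, and a condensed article need not print every scenario.
- **Ambiguous event rates.** One might ask whether 3% and 5% are annual. The end point is fixed at 5 years and the text refers to an overall rate. Annual rates would give about 71 and 113 events and over 99.9% power for a hazard ratio of 4.0, which contradicts the stated 70% and 90%. The cumulative reading is already the natural one.
- **Null results read as exclusion.** Nothing in the article plans to infer absence of effect from a non-significant result.
- **The sample size itself is wrong.** The hazard-ratio-4.0 example holds. If 5-year MACE exceeds 5%, smaller hazard ratios become detectable than those in the table.

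**Conclusion.** The concern holds as a misdescribed detectable effect. In the formula that reproduces the plan's 70% and 90%, the stated minimum hazard ratios of 3.0 and 2.3 have 51% and 49% power, or 55% to 60% by simulation. They are significance thresholds, and they do not meet the standard of the sentence before them. At 80% power the corresponding minima are 4.7 and 3.3.

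This rests on 15 and 25 events among 500 patients, 32% prevalence, 1-sided alpha 0.025 and a single binary factor under proportional hazards. The first three are the plan's own conditions; the last is the setting of the formula that matches its figures. The finding concerns what the article says the study can detect. It does not touch the end point, the test level, the planned models or enrolment.

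**What to change.** Replace the sentence on minimum hazard ratios with, for example:

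*For 500 patients with 15 (3%) or 25 (5%) events over 5 years, a risk factor present in 32% and a 1-sided alpha of 0.025, the smallest hazard ratio detectable with 80% power is 4.7 or 3.3 (with 90% power, 6.0 or 4.0).*

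Alternatively, keep 3.0 and 2.3 and label them as the smallest observed hazard ratios that would reach significance, with about 50% power if they are the true values.

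Either change is wording only and leaves enrolment as planned. The one cost is that the detectable effects look less favourable.
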